## 3. Discussion

Since acupuncture was first used for smoking cessation in 1977,^[33]^ it has been recognized for its simple operation and low cost.^[34]^ Recent studies have shown that AA is an alternative option.^[21]^ This study will clarify the efficacy and safety of AA combined with NRT for smoking cessation and suggest clinical evidence to clinicians and policymakers in their decision-making.

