## 2. Methods

### 2.1. Objectives

This pilot study aims to assess the efficacy and safety of AA treatment combined with NRT for smoking cessation comparing NRT alone.

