### 2.3. Design

This study is a randomized, assessor-blinded, pragmatic pilot clinical trial with 2 parallel groups. We intend to investigate the synergic effects of AA treatment on smoking cessation. Eligible participants will be assigned to 1 of 2 groups with a 1:1 ratio. The control group will receive only NRT, and the experimental group will receive AA treatment + NRT. The study period will include 4 week-treatment phase and 3 month-follow-up. The study design flowchart is as shown in Figure 1.

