### 2.5. Sample size calculation

There have been several studies that investigated the additional efficacy of AA comparing conventional treatment (including NRT and counseling).^[21,23,24]^ However, these studies had some limitations such as using laser AA or a retrospective study. With these reasons, we could not quote fully by previous studies. According to Julious’s suggestion,^[25]^ we determined the appropriate sample size for a 2-parallel study was 12, and in consideration of the drop-out rate, we have decided to recruit 20 participants per group.

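### The two-arm pilot can estimate the effect of adding AA to NRT, but not synergy, and its size does not support the promise to clarify efficacy and safety

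*Protocol article*

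**What the plan says.** The formal objective (protocol article, 2.1) is an add-on comparison: "This pilot study aims to assess the efficacy and safety of AA treatment combined with NRT for smoking cessation comparing NRT alone". Section 2.3 describes the design: "This study is a randomized, assessor-blinded, pragmatic pilot clinical trial with 2 parallel groups". It then gives a second aim, "We intend to investigate the synergic effects of AA treatment on smoking cessation", and fixes the arms: "The control group will receive only NRT, and the experimental group will receive AA treatment + NRT".

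Section 2.5 explains that earlier studies could not be fully relied on. It takes the size from a published suggestion: "the appropriate sample size for a 2-parallel study was 12, and in consideration of the drop-out rate, we have decided to recruit 20" per group. It gives no effect size, standard deviation, event rate, power or drop-out figure.

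Under 2.9, participants and practitioners are unblinded and outcome assessors are blinded. Under 2.11.1, the primary outcome is the participant's own count of cigarettes per day, and a urine test at visits 8 to 10 checks cessation. Section 2.12 lists t, Wilcoxon, chi-squared and Fisher tests, judged at P < .05 with no sidedness given.

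The Discussion concludes: "This study will clarify the efficacy and safety of AA combined with NRT for smoking cessation and suggest clinical evidence to clinicians and policymakers".

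**The concern.** Two statements go beyond what the design can deliver.

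1. Synergy means that AA and NRT together do more than the sum of what each does separately. That is an interaction, and two arms that both contain NRT hold no information on it.
2. Clarifying efficacy and safety for clinicians and policymakers implies an answer firm enough to act on. The number of participants was not chosen to give such an answer, and a P value threshold is the only stated basis for one.

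At stake is how the result is read. With the present wording, a P value above .05 invites the conclusion that AA adds nothing, and one below .05 invites the conclusion that AA works, or works synergistically. Neither follows.

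**Working it through.** **Synergy.** Write the mean outcomes as m(0) for no treatment, m(N) for NRT, m(A) for AA and m(NA) for both.

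- Add-on effect of AA over NRT: m(NA) − m(N).
- Interaction: [m(NA) − m(N)] − [m(A) − m(0)].

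The trial observes only m(N) and m(NA). The first bracket can be estimated. The second needs an AA-only arm and a reference arm with neither treatment (or a sham), and neither exists. The same data are therefore compatible with positive, zero or negative interaction, and more participants would not change that.

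**Sample size.** The 12 is a quoted number without inputs, so no power formula can reproduce it. The following describes only what the planned numbers can deliver.

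*Inputs.* n = 20 per arm (2.5), and n = 12 per arm as the lower case if only the base number remains. I assume two-sided alpha of 0.05, equal SDs and a two-sample t test. Differences are in SD units because the article gives no SD.

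*Precision.* Half-width of the 95% interval = t(0.975; 2n − 2) × √(2/n).

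- n = 20: 2.024 × √0.1 = 2.024 × 0.316 = 0.64 SD
- n = 12: 2.074 × √(1/6) = 2.074 × 0.408 = 0.85 SD

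At 20 per arm, an observed difference of zero has an interval of −0.64 to +0.64 SD, so a true difference of 0.5 SD is not excluded. A difference that just reaches P = .05 has an interval of 0 to 2 × 0.64 = 1.28 SD, so its size is almost undetermined.

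*Power of the t test (noncentral t).*

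| | 20 per arm | 12 per arm |
|---|---|---|
| Difference detectable with 80% power | 0.91 SD | 1.20 SD |
| Power at 0.5 SD | 34% | 22% |
| Power at 0.8 SD | 69% | 47% |

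*Abstinence, illustration only.* The Introduction gives 5% success without treatment and says NRT doubles success, hence 2 × 5% = 10%. It also quotes 40% for AA. Exact power of Fisher's test across a range of assumed rates:

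| NRT vs NRT + AA | 20 per arm | 12 per arm |
|---|---|---|
| 10% vs 20% | 7% | 2% |
| 10% vs 30% | 24% | 10% |
| 10% vs 40% | 49% | 23% |

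*Safety.* If an adverse event is never seen in n AA participants, the one-sided 95% upper limit for its rate is 1 − 0.05^(1/n): 13.9% for n = 20 and 22.1% for n = 12.

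**The case against.** The best defence is that the article is modest almost everywhere else. It calls itself a pilot in the abstract, 2.1 and 2.3. It admits in 2.5 that earlier studies could not carry a calculation. It describes AA as adjuvant or additional treatment, and the abstract promises only additional evidence. The formal objective is the add-on contrast, and 2.12 plans no interaction test. On this view, synergic is one loose word and P < .05 a routine convention. Much of this stands. It makes the synergy point a correction of terms within a sound comparison. It does not remove the sentence in 2.3 or the promise in the Discussion, which are what readers will take away.

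A reader might also infer stronger criticisms that the article does not support:

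- *That the trial claims it will show synergy.* Section 2.3 states only an intention to investigate it.
- *That the trial is simply open-label.* Assessors are blinded and cessation is checked by urine test. Assessor blinding protects little when the participant supplies the cigarette count, but urine-validated cessation is less exposed.
- *That the lack of a sham arm is a fault.* A pragmatic add-on comparison without sham is legitimate. Its contrast includes non-specific effects, which the wording should acknowledge.
- *That the plan expects 40% loss.* The figure 1 − 12/20 = 40% is back-calculated and assumes exactly 12 completers are wanted. The sponsor's rate is not given and may stand in the full protocol. Likewise, 12 is sensibly read as per group, since the same sentence ends with a per-group number.
- *That low power is itself an error.* The plan states no power, and a rule-of-thumb size is acceptable for a pilot.

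**Conclusion.** The point holds as a mismatch between stated conclusions and stated design. That synergy cannot be estimated follows from the two arms alone and needs no numerical assumption.

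The efficacy part rests on an assumed two-sided 5% level and a t test with equal SDs. On that basis the difference will be known to about ±0.64 SD with all 20 per arm, and ±0.85 SD with 12. A non-significant result would leave a moderate benefit open. A barely significant one would leave the effect anywhere from nil to more than 1 SD. A much larger observed difference would be evidence that adding AA changes reported smoking, but its size would remain imprecise and would include non-specific effects in an unblinded, self-reported count.

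The abstinence figures are weaker support. The rates come from background statements in different sources, the 40% is for AA rather than AA with NRT, and 2.11.1 ties the abstinence rate to change in cigarette number rather than clearly to a yes/no outcome. The conclusion does not depend on them.

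**What to change.** Three changes of wording:

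1. **Section 2.3.** Replace the reference to synergic effects with *the effect of adding AA to NRT*, matching 2.1. State that for the self-reported cigarette count this includes non-specific effects because participants are unblinded, and that urine-validated cessation is less exposed.
2. **Section 2.12.** Make the between-group difference with its 95% confidence interval the main result, and treat P values as exploratory.
3. **Discussion.** Replace the promise to clarify efficacy and safety with *will give preliminary estimates of the add-on effect, its SD and retention for a definitive trial*.

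No drop-out percentage should be written into 2.5 on the strength of this review; only the sponsor can supply the rate it assumed.

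The changes need no extra participants, visits or measurements. The cost is a more modest stated claim.
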